#### 2.7.1. Study procedure.

Study candidates will be screened during visit 1. Those who meet all the inclusion criteria and none of the exclusion criteria will be invited to participate. Both patient and caregiver must sign the written informed consent, a sine qua non condition for enrollment. Seven study visits will be performed for enrolled patients, and all the information detailed in Table 3 will be gathered.

**Table 3 T3:** Participant timeline.

	Visit 1 (baseline visit)	Visit 2	Visit 2.1	Visit 3	Visit 4	Visit 5	Visit 6
	Screening and enrollment	Start of treatment					End of treatment
	−60/−30 d	Day 0 (Wk 0)	Wk 4 ± 3 d after visit 2	Wk 13 ± 1 wk after visit 2	Wk 26 ± 1 wk after visit 2	Wk 39 ± 1 wk after visit 2	Wk 52 ± 2 wks after visit 2
**Inclusion/exclusion criteria**	✓	✓					
**Written informed consent**	✓						
**Demographic data***	✓						
**Vital signs (BP, HR, T, RR) and body weight**	✓	✓	✓	✓	✓	✓	✓
**Physical examination**	✓	✓	✓	✓	✓	✓	✓
**Neurological examination** ‡	✓	✓	✓	✓	✓	✓	✓
**Neuropsychological assessment** §	✓				✓		✓
**General blood tests** ‖	✓			✓	✓	✓	✓
**Biomarkers:** **24-OH-cholesterol**	✓			✓	✓	✓	✓
**Biomarkers:** **Oxysterols** **Lyso-sm-509**	✓				✓		✓
**EKG**	✓			✓	✓	✓	✓
**Medication dispensing**		✓		✓	✓	✓	✓
**Brain MRI**	✓						✓
**Brain ^18^FDG-PET scan**	✓				✓		✓
**Oculography**	✓				✓		✓
**Abdominal ultrasound**	✓				✓		✓
**Lumbar puncture**		✓†					✓†
**AE recording**	✓	✓	✓	✓	✓	✓	✓
**Concomitant medication recording**	✓	✓	✓	✓	✓	✓	✓
**Patient’s journal**		✓		✓	✓	✓	✓
**Pregnancy test**	✓	✓		✓	✓	✓	✓

AE = adverse event, BP = blood pressure, EKG = electrocardiogram, HR = heart rate, MRI = magnetic resonance imaging, RR = respiratory rate, T = temperature.

(1) Includes genetic diagnosis.

‡ Includes Ataxia Scale (SARA), Dysphagia Scale (EAT-10), Pineda Disability Scale.

§ CDR-SoB: Clinical Dementia Rating-Sum of Boxes Scale; a-BT: Abbreviated Barcelona Test; WAIS-III/WAIS-IV: Weschler Adult Intelligence Scale, Cubes, Symbol Search, and Vocabulary subtests; FCSRT: Free and Cued Selective Reminding Test; Verbal Fluency Score: Semantic and phonemic tasks (category fluency [CF] and letter fluency [LF]); TMT: Trail Making Test A and B; SCWD: Stroop Color and Word Test; BNT: Boston Test, subtests Naming and Semantic Knowledge Test; JLO: Judgement of Line Orientation Test; DEX: Dysexecution Questionnaire; NPI: Neuropsychiatric Inventory; AES: Apathy Evaluation Scale; BDI: Beck Depression Scale; C-SSRS: Columbia Suicide Severity Risk Scale.

‖ Complete blood count, coagulation tests, and Biochemistry (sodium, potassium, calcium, protein, glucose, urea, creatinine, aspartate aminotransferase, alanine aminotransferase, cholesterol, TSH, T4).

† **Lumbar puncture** will be performed to determine CSF biomarkers (i.e., Beta-amyloid, Tau, and phosphorylated Tau) in those patients who agree to undergo this procedure. The investigator must inform patients and caregivers that this procedure is optional and about the risks involved. Patients who accept it will be required to sign a separate and specific written informed consent (both patients and caregivers must sign it).

We estimate it will take approximately 3 months to complete the enrollment procedure. We expect to carry out the study between 2022 and 2024.

By the moment of submitting this manuscript, participant recruitment (patients’ screening visit) was still in progress.

Participant Timeline

The EFV will be provided by the study sponsor and will be acquired through the Pharmacy Department at BUH. The supplied EFV is to be used exclusively in this clinical trial. The Pharmacy Department will have an updated record of the EFV and manage an inventory that will collect all product entries, dispensing, returns, and disposals.

The records will comply with current regulations and guidelines. Once they are completed, they must be signed and dated by the person in charge. The clinical trial pharmacist will be responsible for maintaining all records of the medication used. The EFV does not require any special storage conditions according to the SmPC and should not be used after the expiry date indicated on the label.

It is the investigator’s responsibility to ensure that the necessary measures have been taken for proper EFV disposal, as required by applicable legislation, guidelines, and institutional procedures.

### 2.8. Sample size

We have not performed a formal sample size calculation. Adult NPC is an orphan disease, with an estimated prevalence of 27 patients in Spain in 2019. The principal investigator (PI) currently follows 14 of these patients at the BUH. Therefore, we expect to enroll a total of 14 patients.

### 2.9. Recruitment

The study patients will be recruited from the BUH Neurology Department. The PI will recruit patients chronologically, as they come to the BUH, when they meet the selection criteria specified before, until reaching the 14 expected patients.

### 2.10. Assignment of interventions

#### 2.10.1. Allocation: Sequence generation, concealment mechanism, implementation, and blinding (Masking).

Not applicable. This is a single-arm clinical trial; thus, all enrolled patients will receive the study treatment.

### 2.11. Data collection plan

Data collection will be performed during the study visits from both patient interviews and electronic medical registers and will be introduced in an e-CRF created *ad hoc*. A data curation process will be performed to improve data quality and reduce possible errors.

### 2.13. Data management

An electronic case report form (e-CRF) will be created *ad-hoc* for this study based on Research Electronic Data Capture Consortium platform. It will not collect data that allows patient identification.

Comprehensive data will be collected, including the date of patient enrollment, the date of the first administration of EFV, demographic data, medical history, relevant comorbidities, clinical data, any concomitant medications administered, and the results of the biochemical analyses mentioned before.

The study monitoring will be carried out by a Contract Research Organization (OPTIMAPHARM, https://optimapharm.eu/; accessed on August 1st, 2022).

### 2.14. Statistical methods for analyzing primary and secondary outcomes

We will perform a descriptive analysis of the enrolled patients’ baseline sociodemographic and clinical data as a whole and by study groups.

The primary outcome measure will be evaluated by an analysis of covariance (ANCOVA). Cognitive performance (assessed by the previously described neuropsychological test battery at 52 weeks) will be the dependent variable, and the independent variables will be the study group and the cognitive performance assessed by the CDR-SoB at the baseline visit. Tables will be presented with model coefficients and their 95% confidence intervals (95% CI). Additionally, the effect size will be measured by presenting the marginal means per study group and their standardized difference along with their 95% CI.

Given the exploratory nature of the clinical and biological secondary outcome measures, we will use the same statistical technique outlined for the primary outcome measure. However, either generalized models or non-parametric statistics will be used depending on the distribution of the dependent variable.

R version 3.6 or higher will be used to perform the statistical analysis.

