### 2.7. Outcomes:

Primary and secondary outcomes are summarized in Table 2.

**Table 2 T2:** Summarized outcome measures.

Primary outcome measure	
Change (not deterioration) in cognitive performance at 52 wks of starting treatment with EFV, assessed by:	
CDR-SoB score.	
FCSRT score (to evaluate verbal memory).	
The executive functions as per the following:	
a)a-BT scores in the digit span subtest.	
b)a-BT scores in the mental control subtest.	
c)Scores in verbal fluency subtest: semantic and phonemic tasks.	
d)TMT A and B scores	
e)SCWT scores.	
Secondary outcome measures	
**Clinical**	Neurological: Changes at 52 wks of starting treatment with EFV relative to baseline in:
	SARA score
	EAT-10 score.
	PDS score
	• Neuropsychological (protocol used in clinical practice): In general, the scaled score will be determined for the following questionnaires/scales:
	CDR-SoB^*^ score.
	*Note: It offers a specific score from 0 to 18, the higher the score the greater the severity.
	FCSRT score
	a-BT assessment in the following domains:
	◦Orientation, digit span, automatized sequences (e.g., counting to 20, d of the wk, mo of the yr), comprehension of verbal commands, and comprehension of complex verbal material (i.e., yes-or-no answers to BDAE-based questions) subtests’ scores.
	◦Bilateral gesture-based limb praxis test
	◦Visual memory (i.e., figures)
	◦Reading, repeating, and writing
	◦Mental and written arithmetic
	◦Reciprocal coordination
	◦Unilateral alternating sequences subtest (e.g., serial hand tests, such as fist-palm-side, tapping).
	◦Constructional praxis (drawing copy).
	Verbal Fluency score: Semantic and phonemic tasks
	TMT A and B scores
	SCWT score
	WAIS-III/WAIS IV
	BNT, Naming and Semantic Knowledge subtests’ scores
	JLO Test score.
	DEX questionnaire score.
	NPI score.
	AES score.
	BDI score.
	C-SSRS score.
**Biological**	• Brain ^18^FDG PET–Scan: Quantification of cerebellar, cortical, and thalamic metabolism.
	• Brain MRI: Cortical, white matter, basal ganglia, and cerebellar structures volumetric analysis.
	• Abdominal ultrasound: Spleen size (cm).
	• Oculography: initial speed, amplitude, and execution speed of vertical and horizontal saccades
	• Plasma Oxysterols levels
	• Plasma Lyso-SM-509 level
	• Plasma 24-OH-Cholesterol level
	• Cerebrospinal Fluid (CSF) Beta-Amyloid, Tau, and phosphorylated Tau levels
**Safety**	• Number of adverse events (AEs) according to seriousness, severity, and relationship with EFV.

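### The primary outcome is defined as a yes/no responder status, but the primary ANCOVA never uses it and takes an unspecified test battery as its dependent variable

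*Protocol article*

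**What the plan says.** Table 2 in section 2.7 gives the primary outcome as "Change (not deterioration) in cognitive performance at 52 wks of starting treatment with EFV, assessed by" a list of tests: the CDR-SoB; "FCSRT score (to evaluate verbal memory"); and five executive measures, including "a)a-BT scores in the digit span subtest", "b)a-BT scores in the mental control subtest" and "c)Scores in verbal fluency subtest: semantic and phonemic tasks", followed by TMT A and B and the Stroop test (SCWT).

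The text below Table 2 turns this list into one result per patient. It defines deterioration separately for three items:
- CDR-SoB: a rise of 2 points or more.
- Verbal memory: a fall of 1 SD or more.
- Executive function: a fall of 1 SD or more on two or more of the five executive tests.

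A patient who has not deteriorated on two or more of the three items is a responder, which the text equates with no decay in cognitive performance.

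Section 2.14 sets the analysis: "The primary outcome measure will be evaluated by an analysis of covariance (ANCOVA"). In that model "Cognitive performance (assessed by the previously described neuropsychological test battery at 52 weeks) will be the dependent variable". Only two predictors are listed for it: "the independent variables will be the study group and the cognitive performance assessed by the CDR-SoB at the baseline visit". The promised outputs are model coefficients with 95% CIs, marginal means by study group, and their standardised difference. Responder status is not mentioned.

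**The concern.** An ANCOVA needs one numeric response, and a battery of tests is not one. Section 2.14 promises outputs that suit a continuous score, but neither it nor Table 2 defines such a score. The quantity that section 2.7 does define is binary, and section 2.14 leaves it without an analysis.

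What is at stake is which result counts. With 14 expected patients and several cognitive scores, an analyst following section 2.14 would have to choose a score, or fit one model per score. Nothing in that section says which would be the primary result. A favourable score could be put forward after the data are seen, while the responder rule that was fixed in advance goes unreported or takes second place.

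**Working it through.** **Endpoint and analysis side by side**

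| | Section 2.7 (Table 2 and text below it) | Section 2.14 |
|---|---|---|
| Unit of result | One status per patient | Test battery at 52 weeks |
| Type | Binary (responder or not) | Implied continuous (marginal means, standardised difference) |
| How tests are combined | 2-of-5 executive rule, then 2-of-3 item rule | None stated |
| Baseline | Each item against its own baseline | CDR-SoB at baseline only, whichever score is modelled |

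The two columns do not describe the same quantity. Three further details show that section 2.14 does not imply a single score:
- The raw scores cannot simply be added. Table 2 notes that a higher CDR-SoB is worse, while deterioration on the other two items is a fall.
- CDR-SoB is the only baseline covariate, so the covariate does not identify the intended response.
- CDR-SoB, FCSRT, fluency, TMT and Stroop also appear in Table 2 among the secondary measures, within a larger neuropsychological battery. The section's reference back to a battery could therefore be read more widely than the primary list.

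**How many scores**

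- Split by part: CDR-SoB 1 + FCSRT 1 + digit span 1 + mental control 1 + fluency 2 + TMT 2 + Stroop 1 = 9.
- By the protocol's grouping of five executive tests: 1 + 1 + 5 = 7.
- At item level: 3.

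**What several separate readings would mean**

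The protocol states no alpha. A two-sided 5% level per score is assumed here from its 95% CIs. If the k intervals were independent, the chance that at least one excludes its null value is 1 − 0.95^k:
- k = 3: 1 − 0.95³ = 14.3%
- k = 7: 1 − 0.95⁷ = 30.2%
- k = 9: 1 − 0.95⁹ = 37.0%

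Cognitive scores in the same patients are correlated, and the protocol gives no correlations. A simulation of nine equally correlated one-sample t-tests (n = 14, 20,000 runs) gives 33% at an assumed correlation of 0.3, 28% at 0.5, 21% at 0.7 and 13% at 0.9.

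**What the stated model can produce**

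Section 2.10.1 says the trial has a single arm. The design matrix (intercept, study group, baseline CDR-SoB) then has three columns but rank 2, because the group column equals the intercept. The group coefficient and the standardised group difference cannot be estimated for any score. This is a separate fault. Dropping the group term would still leave open which score is modelled.

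**What the responder endpoint would produce**

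There is no figure in the plan to reproduce, because section 2.8 says no formal sample size calculation was done. With r responders out of n = 14, the exact (Clopper-Pearson) 95% limits are the 2.5% quantile of Beta(r, n − r + 1) and the 97.5% quantile of Beta(r + 1, n − r):
- 7/14: 23.0% to 77.0%
- 10/14: 41.9% to 91.6%
- 12/14: 57.2% to 98.2%
- 14/14: 76.8% to 100%

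That is one primary result in place of seven or nine candidates. The responder counts are illustrations, not predictions.

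**The case against.** The strongest reply is that the protocol does have a combining rule. It does: the text below Table 2 gives one status per patient. A reader who saw only section 2.14 might infer that nothing says how to read the tests together, and the document does not support that. The rule exists; the primary analysis does not use it.

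A second reply is that section 2.14 does not in fact deliver nine primary results, which a reader might also infer. This stands. Nine is the count after splitting fluency and TMT, the protocol's own grouping gives seven, and with one arm the stated model gives no group effect for any of them.

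A third reply concerns the 30% and 37%. A reader might take these as the chance of wrongly declaring efavirenz effective. They are not. The note in Table 1 counts slowing or stopping of decline as success and hopes that patients stay at their baseline level. No true change is therefore the hoped-for outcome, not a null of inefficacy. The figures show only how quickly chance findings accumulate across several intervals.

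Finally, score derivation and multiplicity are often left to a SAP, which is not shown, and the Discussion already concedes that chance cannot be safely excluded and that Phase III confirmation is needed. That would answer a complaint about missing detail. Here, however, section 2.14 does state the dependent variable, in a form that cannot be run as one analysis and that does not match the endpoint in section 2.7.

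**Conclusion.** The concern holds as a mismatch between endpoint and analysis. Section 2.7 defines a binary responder status. Section 2.14 analyses something else, left as an undefined continuous score drawn from seven tests or nine scores. This follows from the text alone and needs no assumption.

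The size of the consequence is less certain. The multiplicity figures depend on an assumed 5% level, on the count chosen and on independence, and they fall as correlation rises. They show why one variable should be named and should not be cited as an error rate for the trial's efficacy claim. Correction is worthwhile but in proportion to a small, single-arm phase II study: it removes room for selective reading, but cannot supply the missing comparator that the Discussion acknowledges.

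**What to change.** In section 2.14, make the responder status already defined in section 2.7 the single primary variable. Report it as the proportion of enrolled patients who are responders, with an exact 95% CI. Report CDR-SoB, FCSRT and each executive score as descriptive change from baseline to 52 weeks with 95% CIs, and state that no primary efficacy claim will be drawn from any one of them. The responder definition itself does not change.

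An alternative would be a new continuous composite of standardised changes. It is a debatable choice, and by itself it would leave the responder endpoint without an analysis.

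The cost is wording only: no new data, visits or patients. The drawback is precision. A binary result on 14 patients has a wide interval (41.9% to 91.6% at 10/14), which is why the continuous component changes should be shown beside it.

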### 2.4. Criteria for discontinuing or modifying allocated interventions

As mentioned before, all enrolled patients will receive EFV + SoC. The EFV will be discontinued if the investigator deems that it poses an unacceptable risk to the patient; the patient withdraws his consent; there is a significant violation of the study protocol; there is a loss to follow-up; or in case a study participant becomes pregnant.

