### 2.16. Analysis population and missing data definition of analysis population relating to protocol nonadherence and any statistical methods to handle missing data

In case of missing data, imputation will be made considering the treatment effects’ estimator is not biased and that an increase in type I error has been avoided. However, assuming that the cognitive impairment will slow down and aiming to ensure the trial’s internal sensitivity (in case of expecting a different evolution of one of the experimental groups), the last observation carried forward technique seems to be a conservative approach to the matter.

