## 3. Discussion

NPC is a complex orphan disease, consisting of an unmet medical need for patients suffering from it. Although there are over 20 ongoing studies on NPC registered in the ClinicalTrials.gov database, conducting clinical trials for assessing new therapeutic options can be quite challenging, given the disease’s low prevalence. Different therapeutic approaches are under study (e.g., Miglustat, Arimoclomol, N-Acetyl-L-Leucine), but, to the best of our knowledge, this is the first clinical trial studying the effects of EFV in adult- and late-juvenile-onset NPC.

As mentioned before, neuronal cholesterol metabolism is key for LTP, which is a major event for synaptic plasticity. The enzyme CYP46A1 hydroxylates the cholesterol and mediates the main pathway for its degradation in the brain.^[9,10]^ Given that NPC1 binds cholesterol and participates in its intracellular mobilization, we hypothesized that NPC1 would have a synapse-specific role in redistributing cholesterol and mobilizing CYP46A1 to the synaptic membrane required for LTP. We believe that the capacity of EFV to activate the CYP46A1 could compensate for NPC1 deficiency and correct synaptic changes, therefore compensating cognitive and psychiatric alterations in patients with NPC. This hypothesis is supported by preclinical data^[12,14]^ suggesting that low-dose EFV may be a promising alternative for NPC patients.

On the other hand, this study has limitations. First, the already mentioned small sample size due to the disease’s low prevalence. Therefore, interpreting the results may be tough, given that we cannot safely exclude that a given outcome happened by chance. Second, it has a single-arm design (absence of a control group). Although justifiable by the natural history of the disease, the unexpectedness of spontaneous improvement, and the lack of expected placebo effects, this type of design has idiosyncratic limitations since it could be argued that responders would have responded equally if treated only with SoC. Furthermore, the absence of a frame of reference for comparison could also make the results hard to interpret.

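### The primary ANCOVA compares study groups in a single-arm trial, so its group coefficient and between-group effect size cannot be estimated

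*Protocol article*

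**What the plan says.** Section 2.14 of the protocol article names ANCOVA as the primary analysis. The dependent variable is cognitive performance at 52 weeks on the neuropsychological battery, and "the independent variables will be the study group and the cognitive performance assessed by the CDR-SoB at the baseline visit". Model coefficients are to be tabulated with 95% confidence intervals, and "the effect size will be measured by presenting the marginal means per study group and their standardized difference along with their 95% CI". Baseline descriptives are also to be split by study group. Secondary outcomes use the same technique, with generalized models or non-parametric statistics as alternatives where the distribution calls for them.

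The design sections describe one arm. Section 2.10.1 states: "This is a single-arm clinical trial; thus, all enrolled patients will receive the study treatment". Section 2.4 agrees: "As mentioned before, all enrolled patients will receive EFV + SoC". The Discussion lists the lack of a control group as a limitation. Nevertheless, section 2.16 defends last observation carried forward with the phrase "in case of expecting a different evolution of one of the experimental groups".

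The text below Table 2 in section 2.7 defines a responder for each patient: no deterioration at week 52 in at least two of three items (CDR-SoB, verbal memory, executive function). Section 2.14 does not say how the responder proportion will be analysed.

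**The concern.** An ANCOVA with a group term estimates a difference between groups. With a single group there is no difference to estimate, so the effect measure that the plan names has no meaning in this design. This is not a detail left to a later document: the article commits to a specific model, and that model does not fit its own design.

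The planned primary efficacy result is at stake. The outcome spans three domains, one of which is built from five tests, and every patient is treated open-label. If the stated analysis is unusable and the responder endpoint has none, the replacement could be picked from many candidates once results are visible. With 14 patients, and a Discussion that concedes chance cannot safely be excluded, that freedom could decide the conclusion.

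**Working it through.** **Inputs.** One arm (sections 2.4 and 2.10.1, Discussion). Planned n = 14 (section 2.8). Model terms: study group and baseline CDR-SoB (section 2.14). Responder definition: section 2.7. Section 2.8 reports no formal sample size calculation, so there is no power or alpha figure to reproduce. The check is therefore one of identifiability.

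**1. The model as written.** For patient *i*,

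y_i = β0 + β1·g_i + β2·b_i + e_i,

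where y is the week-52 score, g the study group and b the baseline CDR-SoB. If study group means treatment arm, g_i = 1 for all 14 patients, and the model becomes

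y_i = (β0 + β1) + β2·b_i + e_i.

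Only the sum β0 + β1 is identified; β1 alone is not. The design matrix [1, g, b] has 3 columns and rank 2. A numerical check with simulated baseline values gave a smallest singular value of about 2 × 10⁻¹⁶, which is zero to machine precision.

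**2. In the named software.** In R (4.3.3; the plan asks for 3.6 or higher), a linear model with a one-level group factor stops with an error saying that contrasts need two or more levels. With the group coded as a constant, its coefficient is returned as NA.

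**3. What is lost and what remains.**

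| Planned quantity | Status with one arm |
|---|---|
| Group coefficient and 95% CI | not estimable |
| Comparison of marginal means between groups | does not exist |
| Standardized difference and 95% CI | does not exist |
| Intercept, baseline CDR-SoB slope | estimable once the group term is dropped (14 − 2 = 12 residual df) |
| One overall adjusted mean | estimable, not a treatment effect |

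**4. What a one-sample analysis would deliver at n = 14.** The Clopper-Pearson limits for x responders are the 0.025 quantile of Beta(x, n − x + 1) and the 0.975 quantile of Beta(x + 1, n − x). For x = n the upper limit is 1 and the lower limit is 0.025^(1/14) = 0.768. The counts below are hypothetical; the article gives none.

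| Responders | Proportion | Exact 95% CI |
|---|---|---|
| 7/14 | 50% | 23% to 77% |
| 12/14 | 86% | 57% to 98% |
| 14/14 | 100% | 77% to 100% |

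For a mean change from baseline, the 95% half-width is t(0.975, 13)/√14 = 2.160/3.742 = 0.577 SD of the change.

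**5. Why a test cannot simply be substituted.** A test needs a reference rate of non-deterioration, p0, and the article gives none. Assuming p0 = 0.5, the smallest cut-off with one-sided alpha at or below 0.05 is 11/14 (alpha 0.029). Assuming p0 = 0.8, it is 14/14 (alpha 0.044). With an assumed true rate of 0.90, power is 0.956 and 0.229 respectively. An unsourced p0 would therefore decide the result.

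**The case against.** **Another meaning of group.** The rank argument assumes that study group means treatment arm. Three subsets would give a column that varies: adult-onset against late juvenile-onset patients (note to section 2.2.1), patients whose dose is increased after the biomarker check (section 2.3), and patients who have the optional lumbar puncture (section 2.2.2 uses the word group for them). The assumption has to be stated, but none of the three rescues the text. None is called a study group, the dose-increased subset forms after baseline, and no contrast between such subsets estimates the effect of efavirenz.

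**Something can still be estimated.** A reader might infer that the plan yields no primary estimate at all. The article does not support that. Section 2.14 promises model coefficients, and an intercept and baseline slope can be fitted once the redundant column is dropped. This objection stands, and it limits the point to between-group quantities.

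**The consequence is not inevitable.** A reader might also infer that the primary analysis will be chosen after the data are seen. Section 3.1 places the trial in screening in August 2022, so an amendment or a statistical analysis plan could settle the matter before week-52 results exist. This stands too: the risk is possible, not demonstrated.

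**A leftover from a controlled design.** The plural groups in sections 2.14 and 2.16 may suggest that the text was carried over from a two-arm protocol. The article does not say where it came from, and the point does not depend on it.

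**Conclusion.** The point holds for between-group quantities. On the reading that study group means treatment arm, the primary model in section 2.14 has one redundant column out of three, and every effect measure that depends on comparing groups is unavailable, for the primary outcome and for the secondary outcomes that share the technique. What survives describes one treated cohort and does not isolate an effect of efavirenz. Because the responder endpoint also has no stated analysis, the article as published contains no workable primary efficacy analysis. The rank result does not depend on the outcome data, and dropouts would not change it. The conclusion does not extend to saying that nothing can be estimated, or that a post hoc choice has been or will be made.

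**What to change.** Make the change before any week-52 data are analysed.

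- **Delete** from section 2.14 the study-group term, the marginal means per group, the standardized difference and the split of baseline descriptives by group. Delete from section 2.16 the reference to experimental groups.
- **Primary:** the proportion of responders at week 52, as defined in section 2.7, with an exact Clopper-Pearson 95% confidence interval. Declare it as estimation only, because no reference rate is given.
- **Supportive:** for each component of the primary outcome, the mean change from its own baseline to week 52 with a 95% confidence interval and a standardized mean change.
- **Secondary outcomes:** one-sample changes in the same way, keeping section 2.14's option of generalized or non-parametric methods, which does not depend on having groups.

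The cost is a wording amendment. Replacing the primary analysis may count as a major change, which section 2.22 sends for IRB approval. The statistical analysis plan is not shown, so whether it also needs changing is unknown. The responder definition and the visit schedule in Table 3 already supply the data, so no extra patients or assessments are needed.

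### The primary model yields a week-52 mean adjusted for baseline CDR-SoB, so for the FCSRT and the executive tests it cannot show the change from baseline that defines the outcome

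*Protocol article*

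**What the plan says.** Section 2.14 of the protocol article describes the primary analysis as an ANCOVA. The outcome variable is given as "Cognitive performance (assessed by the previously described neuropsychological test battery at 52 weeks) will be the dependent variable". The covariates are given as "the independent variables will be the study group and the cognitive performance assessed by the CDR-SoB at the baseline visit". Results are to be shown as model coefficients, marginal means per study group and a standardized difference between groups. On the secondary measures it states: "Given the exploratory nature of the clinical and biological secondary outcome measures, we will use the same statistical technique outlined for the primary outcome measure", with this qualification: "However, either generalized models or non-parametric statistics will be used depending on the distribution of the dependent variable".

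The outcomes themselves are framed as change:

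- Section 1.3, Table 1: the note to the primary objective hopes that patients will still be at their starting cognitive level after one year. The secondary clinical and biological objectives are all worded as evaluating change.
- Section 2.7, Table 2: the primary outcome is change, in the sense of no deterioration, at week 52. The neurological outcomes are introduced by "Changes at 52 wks of starting treatment with EFV relative to baseline in" and then list SARA, EAT-10 and PDS.
- Section 2.7, text below Table 2: deterioration in CDR-SoB, verbal memory and executive function is each defined against the patient's own baseline. A responder is a patient with no deterioration in two or more of these three domains.

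Section 2.10.1 confirms a single arm, and section 2.8 expects 14 patients.

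**The concern.** Sections 1.3 and 2.7 ask whether patients hold their baseline level. Section 2.14 specifies a model that, for most of the primary battery, never uses that level. The only baseline value named is CDR-SoB, including where the dependent variable is a memory or executive test.

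In a two-arm trial this would mainly cost efficiency, because the group contrast would still answer a question about treatment. With one arm there is no contrast, and the comparison with the patient's own baseline is the only one left. If that is missing, the primary analysis cannot support or refute the stated hypothesis for two of its three domains.

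**Working it through.** The protocol states no sample-size or precision figure, so there is nothing to reproduce. Three checks were made.

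**1. What the planned model can estimate.** The design has three columns for 14 patients: intercept, study group and baseline CDR-SoB. With one arm, the group column is the same for everyone and duplicates the intercept. The matrix has 3 columns and rank 2. Neither the group coefficient nor the standardized group difference can be estimated. What remains is

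week-52 value = a + b × (baseline CDR-SoB − its mean) + error.

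In least squares with a centred covariate, a is the sample mean of the week-52 values. The marginal mean is therefore the week-52 mean.

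**2. Whether the fit responds to change.** Two artificial datasets of 14 patients were built with identical week-52 values and identical baseline CDR-SoB, differing only in the test's own baseline (arbitrary units).

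| | Dataset A | Dataset B |
|---|---|---|
| Planned model: marginal mean at week 52 | 16.14 | 16.14 |
| Planned model: slope on CDR-SoB | −0.08 | −0.08 |
| Mean change from own baseline | 0.02 | 2.11 |

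The planned output is the same for a cohort that stayed level and for one that moved by about two units. This holds for any measure whose own baseline is not in the model. CDR-SoB is the exception: its own baseline is the covariate, so the change can be recovered by subtracting the baseline mean, although section 2.14 does not say to do so.

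**3. Precision.** Inputs: n = 14 (section 2.8). The correlations are assumptions, since the protocol gives none. The SD is taken as equal at both times, and results are in units of that SD.

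Mean change from own baseline: half-width = t(0.975; 13) × √(2(1 − ρ)) / √14, with t = 2.160 and √14 = 3.742.

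- ρ = 0.5: 2.160 × 1.000 / 3.742 = 0.58
- ρ = 0.7: 2.160 × 0.775 / 3.742 = 0.45
- ρ = 0.8: 2.160 × 0.632 / 3.742 = 0.37
- ρ = 0.9: 2.160 × 0.447 / 3.742 = 0.26

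Planned week-52 mean adjusted for CDR-SoB: half-width = t(0.975; 12) × √(1 − r²) / √14, with t = 2.179 and r the correlation of the week-52 value with baseline CDR-SoB.

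- r = 0: 0.58
- r = 0.3: 0.56
- r = 0.5: 0.50

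The two sets of intervals belong to different quantities, so their ratio is not a loss of efficiency for one estimand. At ρ = 0.5 the change interval is no narrower than the planned one.

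**The case against.** Five arguments can be made for the plan.

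- *ANCOVA on a final value is standard.* With a comparator and the measure's own baseline as covariate, it gives the same group effect as an analysis of change. That is correct, so a week-52 dependent variable is not a fault in itself. Here the comparator is absent for every test, and the own baseline is absent for the FCSRT and the executive tests.
- *Section 2.7 already fixes change from own baseline through the responder definition.* It does, and the definition is usable. But section 2.14 never analyses it. An ANCOVA reporting marginal means and a standardized difference is not an analysis of a yes/no responder status.
- *The secondary measures are not expressly tied to CDR-SoB.* This stands. A reader might infer that spleen size, PET and oxysterols will all be adjusted for baseline CDR-SoB. The protocol does not say that. The same technique may simply mean ANCOVA with each measure's own baseline, and generalized or non-parametric methods are allowed. Table 2 also lists the biological measures as levels or quantities; their change wording is in Table 1. For these outcomes the covariate is ambiguous, not wrong. Nor does the point reach every outcome: adverse events are descriptive (section 2.15).
- *Intermediate visits need not be used.* A reader might infer that ignoring them is an error. The stated time point is week 52, so a week-52 analysis matches it. Table 3 has no intermediate brain MRI or lumbar puncture, and the puncture is optional. Last observation carried forward (section 2.16) brings in earlier values only where week 52 is missing. A longitudinal model is an option, not a correction.
- *Details belong in the analysis plan.* Often so, but the article itself fixes the dependent variable and covariates of the primary model.

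**Conclusion.** The point holds for the primary outcome. As written, section 2.14 gives a week-52 mean for the FCSRT and the executive tests and cannot show whether patients declined from baseline. This follows from the stated model and the single arm, and needs no assumed figure. For the secondary measures it holds only if the reference to the same technique is read as carrying over the CDR-SoB covariate; otherwise their covariate needs stating.

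A reader might also infer a large, fixed loss of precision. The documents do not support one, because the baseline-to-week-52 correlation is not given. Over assumed values of 0.5 to 0.9 the half-width for mean change runs from 0.58 down to 0.26 SD. The reason to change the plan is the mismatch between outcome and estimate; tighter intervals are a possible benefit.

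**What to change.** In section 2.14, and in the analysis plan if one exists:

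1. Remove the study-group term and the between-group standardized difference.
2. For each cognitive test, estimate the mean change from its own baseline to week 52 with a 95% CI. Where a model is used, take the change as dependent variable and the measure's own centred baseline as covariate, so that the intercept is the mean change.
3. For the primary outcome, report the proportion of responders as defined in section 2.7 with an exact 95% CI.
4. State that secondary clinical and biological measures are analysed as change from their own baseline, keeping the generalized or non-parametric alternatives where distributions require them.
5. Optionally, add a mixed model using the intermediate visits as a supportive analysis where such visits exist, which excludes brain MRI and CSF.

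The cost is revised wording and a little programming. Table 3 already schedules the cognitive battery at baseline and week 52, so no further measurement is needed. The change should be made before the week-52 data are analysed. It does not supply a comparator: the limitation that section 3 acknowledges, that responders might have done as well on standard care alone, remains.
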